## Statement of Compliance

This study will be carried out in accordance with Good Clinical Practice (GCP) as required by the following:

- U.S. Code of Federal Regulations dealing with clinical studies (45 CFR 46 and 21 CFR including parts 50 and 56 concerning informed consent and Institutional Review Board [IRB] regulations).
- Colorado State University IRB
- Nepal Health Research Council (NHRC)
- Completion of Human Subjects Protection Training

<http://grants.nih.gov/grants/guide/notice-files/NOT-OD-01-061.html>

<http://cme.cancer.gov/c01/>

---

**List of Abbreviations**

|               |                                                                  |
|---------------|------------------------------------------------------------------|
| AE            | Adverse Event                                                    |
| AH            | Anandaban Hospital                                               |
| AUC           | Area under the ROC Curve                                         |
| BL            | Borderline Lepromatous Leprosy                                   |
| BP            | Blood Pressure                                                   |
| BT            | Borderline Tuberculoid Leprosy                                   |
| CD            | Compact Disk                                                     |
| CFR           | Code of Federal Regulations                                      |
| CMI           | Cell-Mediated Immunity                                           |
| CRF           | Case Report Form                                                 |
| DCC           | Data Coordinating Center                                         |
| DMID          | Division of Microbiology and Infectious Diseases                 |
| DRF           | Data Resolution Form                                             |
| DTH           | Delayed Type Hypersensitivity                                    |
| eCRF          | Electronic Case Report Form                                      |
| ENL           | Erythema Nodosum Leprosum                                        |
| ER            | Emergency Room                                                   |
| FDA           | Food and Drug Administration                                     |
| FPR           | False Positive Rate                                              |
| FWA           | Federal-Wide Assurance                                           |
| GCP           | Good Clinical Practice                                           |
| GEE           | Generalized Estimating Equations                                 |
| HRC           | Human Research Committee                                         |
| IB            | Investigator's Brochure                                          |
| ICF           | Informed Consent Form                                            |
| ICH           | International Conference on Harmonisation                        |
| IEC           | Independent or Institutional Ethics Committee                    |
| IMB           | Internal Monitoring Board                                        |
| IND           | Investigational New Drug                                         |
| INF- $\gamma$ | Interferon-gamma                                                 |
| IRB           | Institutional Review Board                                       |
| ISM           | Independent Safety Monitor                                       |
| LAM           | Lipoarabinomannan                                                |
| LL            | Lepromatous Leprosy                                              |
| LP            | Lepromatous Leprosy Patient                                      |
| MDT           | Multidrug Treatment                                              |
| MLCwA         | M. leprae Cell Wall Antigen                               |
| MLSA          | M. leprae Soluble Antigen                                 |
| MLSA-LAM      | M. leprae Soluble Antigen minus LAM and other Lipoglycans |
| MPA           | Multiple Project Assurance                                       |
| MO            | Medical Officer                                                  |
| MOO           | Manual of Operations                                             |
| MRL           | Mycobacteria Research Laboratory                                 |
| N             | Number (typically refers to subjects)                            |
| NCR           | No Carbon Required                                               |
| NHRC          | Nepal Health Research Council                                    |

**List of Abbreviations - *continued***

|       |                                                       |
|-------|-------------------------------------------------------|
| NIAID | National Institute of Allergy and Infectious Diseases |
| NIH   | National Institutes of Health                         |
| ORA   | Office of Regulatory Affairs                          |
| PPD   | Purified Protein Derivative                           |
| PI    | Principal Investigator                                |
| PO    | Project Officer                                       |
| Prn   | Pro re nata (as needed)                               |
| QA    | Quality Assurance                                     |
| QC    | Quality Control                                       |
| OHRP  | Office of Human Research Protection                   |
| ROC   | Receiver Operating Characteristic                     |
| SAE   | Serious Adverse Event                                 |
| SC    | Study Coordinator                                     |
| SMC   | Safety Monitoring Committee                           |
| SPA   | Single Project Assurance                              |
| SPA   | Soluble Protein Antigen                               |
| SA    | Soluble Antigen                                       |
| SOP   | Standard Operating Procedure                          |
| TB    | Tuberculosis                                          |
| TD    | Tuberculoid Leprosy Patient                           |
| TLMI  | The Leprosy Mission International                     |
| TPR   | True Positive Rate                                    |
| TT    | Tuberculoid Leprosy                                   |
| WHO   | World Health Organization                             |

## Protocol Summary

**Title:**

Two New Leprosy Skin Test Antigens: MLSA-LAM and MLCwA; Phase II Study in a Leprosy-Endemic Region

**Phase:**

Phase II Clinical Study

**Population:**

This study will be conducted in Kathmandu, Nepal. It will be divided into three stages: A, B, and C (Stage C will be subdivided into two parts; Stage C-1 and Stage C-1b). Study participants will total 260, with the following health status:

Stage A: 10 healthy non-exposed participants

Stage B: 90 healthy non-exposed participants

Stage C-1: 80 total participants

- 20 borderline lepromatous/lepomatous (BL/LL) leprosy patients
- 20 borderline tuberculoid/tuberculoid (BT/TT) leprosy patients
- 20 healthy contacts of BL/LL leprosy patients\*
- 20 TB patients

Stage C-1b: 80 total participants

- 20 borderline lepromatous/lepomatous (BL/LL) leprosy patients
- 20 borderline tuberculoid/tuberculoid (BT/TT) leprosy patients
- 20 healthy contacts of BL/LL leprosy patients\*
- 20 TB patients

Participants will be either male or female; however, not less than one-third will be recruited from either gender, overall. Each will be between the ages of 18 and 60 years old, with a weight greater than 30 Kg (66 lbs) for females, and 38 Kg (83 lbs) for males. All will be Nepali residents, including expatriates from India. Participants must not be concurrently enrolled in a separate clinical trial or have participated in prior stages of this clinical trial. All subjects screened for the study and found to have leprosy or tuberculosis will be treated or referred for treatment as per standard hospital procedure.

\* A leprosy contact is defined as a co-inhabitant of a leprosy patient for a duration of at least six months, and within 6 months prior to study enrollment, or a person who has been professionally

exposed to leprosy for a duration of at least 5 years, and within 6 months prior to enrollment. (Enrollment of contacts of leprosy patients for Stages C-1 and C1b will include only co-inhabitants of BL/LL leprosy patients. )

**Number of Sites:**

Three campuses have been identified in Kathmandu, Nepal for participant recruitment for stages A and B, and four additional campuses have been identified in Kathmandu or Lalagadh for stage C (see Appendix C, Volunteer Breakdown and Estimated Timeline for Completion of Testing, and Section 5.1, "Selection of the Study Population"). Additional campuses/hospitals may also be selected to participate.

**Study Duration:**

Individual volunteers' participation in each stage of the study will last for 7 days ( $\pm 1$  day). If induration greater than 10 mm is observed at any site during the first 7 days post injection, an additional study visit will occur at 28 days. Total time involvement for each participant for all visits is approximately 5.0 hours.

**Description of Agent or Intervention:**

The drug substances to be tested are the soluble proteins of *M. leprae* [MLSA, *M. leprae* soluble antigen with minimal amounts of immunosuppressive lipoglycans, which are mostly lipoarabinomannan (LAM)], called MLSA-LAM, and the cell wall-associated proteins of *M. leprae*, called MLCwA. The active ingredients of these two intradermal skin test antigens are protein antigens of *M. leprae*.

**Objectives:**

The overall objective is to evaluate two new leprosy skin test antigens as diagnostic-epidemiological tools designed to measure the incidence of leprosy infection in a leprosy endemic area.

**Primary:**

- To evaluate the safety of these two new leprosy skin test antigens
- To estimate the specificity and sensitivity of these skin test antigens in detecting *M. leprae* infection by:
  - Selecting a dosage of the MLSA-LAM and MLCwA antigens that causes minimal induration in healthy non-exposed subjects
  - Selecting a size of induration that will serve as a definition of a positive skin test reaction for MLSA-LAM and MLCwA in leprosy patients
  - Comparing the proportion of positive skin test reactors in healthy subjects to the proportion in BT/TT and BL/LL leprosy patients, contacts of leprosy patients, and tuberculosis patients

**Secondary:**

- To compare the mean size of induration in response to each test antigen in healthy subjects versus BT/TT and BL/LL leprosy patients, contacts of leprosy patients, and tuberculosis patients as a measure of specificity and sensitivity
- To compare the specificity and sensitivity of the two new antigens with tuberculin/PPD (purified protein derivative), in patients with clinical leprosy, contacts of leprosy patients, and healthy, unexposed subjects (non-patient contacts)
- To quantify the release of interferon-gamma (IFN- $\gamma$ ) from lymphocytes in whole blood from leprosy patients, leprosy patient contacts, TB patients, and healthy non-exposed subjects, following *in vitro* stimulation with leprosy skin test antigens and PPD, using the QuantiFERON-CMI kit (Cellestis Limited, Valientia, California). Results will be compared to the magnitude of the skin test response.
- To determine if antibodies against a *M. leprae* specific antigen, Phenolic Glycolipid – I (PGL-I) are present in serum from leprosy patients, leprosy patient contacts, TB patients, and healthy non-exposed subjects, using a lateral flow immunodiffusion rapid test kit provided by [name] [name], Seoul, South Korea. Results will be compared to the magnitude of the skin test response.

## Schematic of Study Design:

**Stage A: Safety Study in Non-Contacts (Ramping)**

| Stage | Group | Sample/Size       | Antigens                              | Dose                            | Intervention*                                                                                                                                             |
|-------|-------|-------------------|---------------------------------------|---------------------------------|-----------------------------------------------------------------------------------------------------------------------------------------------------------|
| A     | 1     | 5
Non-Contacts | MLSA-LAM
MLSA-LAM
PPD
Saline | 1.0 µg
0.1 µg
5 TU
N/A | Day –10 to –1: Recruitment
Day 0: Consent, Physical Exam, Pregnancy Test, History, Administer Antigens (~15 minute)
Day 2 (45-51 h): Reading |
|       | 2     | 5
Non-Contacts | MLCwA
MLCwA
PPD
Saline       | 1.0 µg
0.1 µg
5 TU
N/A | Day 3 (69-75 h): Reading
Day 25 to 31: Reading for positive reactors                                                                                   |

\* Adverse Event assessment occurs at each reading time point.

Upon completion of Stage A, the Safety Monitoring Committee (SMC) will review the data and a report will be sent to DMID, NHRC, and CSU IRB. Stage B will proceed upon approval from each of these authorities.

**Stage B: Safety Study in Non-Contacts (Full-Scale)**

| Stage | Group | Sample/Size        | Antigens                              | Dose                            | Intervention*                                                                                                                                             |
|-------|-------|--------------------|---------------------------------------|---------------------------------|-----------------------------------------------------------------------------------------------------------------------------------------------------------|
| B     | 1     | 45
Non-Contacts | MLSA-LAM
MLSA-LAM
PPD
Saline | 1.0 µg
0.1 µg
5 TU
N/A | Day –10 to –1: Recruitment
Day 0: Consent, Physical Exam, Pregnancy Test, History, Administer Antigens (~15 minute)
Day 3 (69-75 h): Reading |
|       | 2     | 45
Non-Contacts | MLCwA
MLCwA
PPD
Saline       | 1.0 µg
0.1 µg
5 TU
N/A | Day 6 to 8: Reading
Day 25 to 31: Reading for positive reactors                                                                                        |

\* Adverse Event assessment occurs at each reading time point.

Upon completion of Stage B, the SMC will review the data and a report will be sent to DMID, NHRC, and CSU IRB. Stage C will proceed upon approval from each of these authorities. Size and frequency of reactions will be a consideration in determining the use of one or both antigens as well as antigen dosages, in Stage C-1.

**Stage C-1: Safety Study in Target Populations**

| Stage | Group | Sample/Size                                                       | Antigens                 | Dose   | Intervention                                                                                                    |
|-------|-------|-------------------------------------------------------------------|--------------------------|--------|-----------------------------------------------------------------------------------------------------------------|
| C-1   | 1     | 20
Contacts of BL/LL leprosy patients
(co inhabitants only) | MLSA-LAM
MLCwA
PPD | 1.0 µg | Day –10 to –1: Recruitment                                                                                      |
|       | 2     | 20
BL/LL leprosy patients                                      |                          | 1.0 µg | Day 0: Consent, Physical Exam, Pregnancy Test, History, Blood Sampling, Administer Antigens (~15 minute) |
|       | 3     | 20
BT/TT leprosy patients                                      |                          | 2 TU   | Day 2 to 4: Reading                                                                                             |
|       | 4     | 20
TB patients                                                 |                          |        | Day 6 to 8: Reading
Day 25 to 31: Reading for positive reactors                                              |

In order to further assess the safety of skin test antigens in individuals who are more likely to present with a robust skin test response to the antigens, a small sample of 20 individuals from each group of the eventual target populations (healthy contacts of BL/LL leprosy patients, BL/LL leprosy patients, BT/TT leprosy patients, and TB patients) will receive the high dose (1.0µg) of each test antigen, and a 2TU dose of tuberculin/PPD. (Based on findings from preliminary testing of participants enrolled in Stage C-1, Tuberculin/PPD dose has been decreased from 5TU to 2TU for the remainder of Stage C-1 and for Stage C-1b.) Data will be reviewed by the SMC, and a report will be sent to DMID, NHRC, and CSU IRB.

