### **3.3 Intervention and Doses being Evaluated**

Depending on the study stage, each individual will receive two 100 µl intradermal injections of titrated doses, or a single dose, of one or both of the two skin test antigens in concentrations of 1 µg protein content/ml and 10 µg protein/ml in the sterile diluent, one injection of 0.9% sodium chloride (sterile, approved for human use, Abbott Laboratories) in Stages A and B only, and one 100 µl injection of tuberculin/PPD Tubersol® 5TU; Aventis Pasteur Inc., Swiftwater, PA in Stages A and B and Tuberculin PPD RT 23 SSI, 2T.U./0.1 ml, solution for injection, Statens Serum Institute, Copenhagen, Denmark in Stages C-1 and C-1b. All injections will be in 0.1 ml volumes, resulting in 0.1µg and 1.0µg doses of test antigens, respectively. The concentration ranges to be tested are based on results of our Phase I study (see p. 12), previous skin testing in humans with Rees' antigen (optimum dosage is 1 µg) as well as our skin test results in guinea pigs.

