Stage C: Upon completion of Stage B, and with approval from DMID, NHRC, and CSU IRB (no sooner than 4 days after the final reading of Stage B), 160 Nepali individuals (including expatriates from India) will be studied in Stage C. This stage is broken down into two parts: Stage C-1 and Stage C-1b, in which 80 subjects from four high risk groups will be studied in each Stage to measure the safety and/or reactivity of the antigens at the high dose (1.0µg) and low dose (0.1µg), respectively. In addition, each subject will provide a 5ml tube of heparinized blood for the laboratory personnel to perform a QuantiFERON-CMI test using leprosy antigens and a 3ml serum separator tube of blood to perform the Rapid PGL-I Antibody Test.

Stage C-1: In order to assess the likelihood of large ulcerating reactions in subjects in higher risk groups, we will first assess the safety of the injections in 80 subjects (20 from each group, except healthy non-contacts) before enrolling any additional subjects. Each individual will receive three 100µl injections (one of each high dose from each test antigen, and one of 2TU Tuberculin/PPD). The injections will be administered as previously described for Stage A, with one exception: the test sites will be at 1.5 inches, and 3.5 inches below the bend of the elbow on one arm and 3.5 inches below the bend of the elbow on the other arm, allowing a total of three injection sites. Each subject will be

randomly assigned one template for antigen administration (see Section 6, “Randomization/Enrollment/ Blinding Procedures”). Safety data will be collected and reviewed by the SMC, and their report will be forwarded to DMID, NHRC, and CSU IRB.

Stage C-1b: To further assess the reactivity of the skin test antigens, the low dose of each antigen will be administered to 80 subjects (20 from each group, except healthy non-contacts) exactly as stated in Stage C-1.

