#### **9.1.2 Control Products: Saline and Tuberculin/PPD®**

Two control products will be used in this study: (1) Saline, 0.9% NaCl, sterile, approved for human use (Abbott Laboratories Inc., Abbott Park, IL); and, (2) Tubersol®, 5TU dose (Aventis Pasteur Inc., Swiftwater, PA) in Stages A and B and Tuberculin/PPD RT 23 SSI, 2TU dose (Statens Serum Institute, Copenhagen, Denmark) in Stages C-1 and C-1b. Vials will contain 1 or 1.5ml total volume. Upon receipt by DMID, vials will be relabeled according to the randomized template described above (Section 9.1.1, "Formulation, Packaging, and Labeling").

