At the end of each training day, each skin test administrator will be given the opportunity to administer an actual tuberculin/PPD skin test with Tubersol® (Aventis Pasteur Inc., Swiftwater, PA) in training for Stages A, B and C-1 or RT 23 SSI (Statens Serum Institute, Copenhagen, Denmark) for Stage C-1b to at least three consenting volunteer leprosy health workers at Anandaban. The trainee's skin test administration technique will be observed and checked by the trainer using a procedural checklist. Seventy-two hours later, the trainees will record the readings from all of the volunteer leprosy health workers who had received tuberculin/PPD. Every trainee will read each reaction several times and the results will be recorded so that the reader's consistency can be assessed. The trainer will also read each of the volunteers' skin test reactions. Variation from the trainer's readings will be plotted on a standard correlation table, as recommended by the International Union against Tuberculosis and Lung Disease. The correlation chart will be used to identify systematic variations between the trainee's and the trainer's readings. Variations from the trainer's readings should not exceed 1 mm. Trainees whose skin test readings vary from the trainer's on average more than 2 mm will not be invited to participate in the study.

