### **9.3.3 Dosage of Investigational Product**

For Stage A and B, each individual will receive two injections of titrated doses of one of the two skin test antigens (in concentrations of 0.1 µg and 1.0 µg in 100 µl sterile diluent, 0.9% NaCl, approved for human use, Abbott Laboratories), one injection of 100 µl 5TU tuberculin/PPD Tubersol®; Aventis

Pasteur Inc., Swiftwater, PA, and one injection of 100µl diluent. For Stage C-1 and C-1b, each individual will receive each of the two skin test antigens at the high dose (1.0µg) only or low dose (0.1µg) only, respectively; and 2TU tuberculin/PPD, RT 23 SSI, Statens Serum Institute, Copenhagen, Denmark.

All injections will be in 0.1ml volumes from vials containing 0.5, 1.0 or 2.0 ml total. All injections will be made within 8 hours of the vials being opened. During this maximum 8 hour period cold storage (2-8°C) will be maintained. The concentration ranges to be tested are based on results of our Phase I study (see p. 12), previous skin testing in humans with Rees' antigen (optimum dosage is 1.0µg in 100µl), as well as our skin test results in guinea pigs.

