### 13.3 Study Design

This is a prospective study where the participants all receive the same set of antigens, but are randomized to receive them in different patterns, that is, according to different “templates”. The participants do not know which template is used and the readers, or evaluators are also blinded to the pattern of antigen delivery. Stages A and B randomized participants to only a single study antigen, at two doses for each volunteer, plus PPD and saline. Schemas for stages A plus B and C follow.

[figure not shown]

Volunteers in stage C-1 will receive both leprosy skin test antigens at the high dose of 1µg per 100µl and PPD at 2TU, while volunteers from stage C-1b will receive the same antigens at the low dose of 0.1µg per 100µl and PPD at 2TU. Since three test sites are required as compared to four in Stage A and B, they will be reassigned (2 sites on the first arm and one on the second arm), and administration templates will be randomized to different administration patterns. For Stage C-1 and C-1b, there will be 20 subjects from each study group, except healthy non-contacts (contacts of leprosy patients; BT/TT and BL/LL leprosy patients; and, tuberculosis patients).

[figure not shown]

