### 13.7 Participant Enrollment and Follow-Up

A total of 260 subjects will be recruited for this trial, 10 subjects for Stage A, 90 subjects for Stage B, and 160 subjects for Stage C (80 each in C-1 and C-1b). The total estimated duration of recruitment of subjects to participate in this study is expected to be no less than 1 month and no greater than 1 year for each stage. (Stage A, B, and C-1 was completed prior to the amendment of this protocol.) Completion of Stage C-1b is expected to take approximately 3 months. Total involvement of an individual participant from administration of study product to final follow-up is expected to be no longer than 28 days.

Seven clinical sites have been selected to participate in this clinical study. Stages A and B were performed at one or more of the following Kathmandu campuses in Nepal: Lalitpur Nursing Campus, Sanepa, Kathmandu; The Central Department of Microbiology, Tribhuvan University, Kirtipur, Kathmandu; and The Institute of Medicine, Tribhuvan University, Maharajgunj, Kathmandu. Stages C-1 and C-1b will be performed at some or all of the above mentioned Kathmandu campuses and/or these additional campuses: AH, Patan Hospital TB Clinic, Lalagadh Leprosy Hospital, and Green Pastures Leprosy Hospital. Other campuses/hospitals may also be selected to participate.

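### Five sections give Stage C-1 tuberculin as 2 TU although early C-1 subjects had 5 TU, and a PPD accuracy pair joining 5 TU non-contacts to 2 TU Stage C subjects cannot separate group from preparation

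*Protocol*

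**What the plan says.** Stages A and B, which hold all the healthy non-contacts, used Tubersol at "5TU dose (Aventis Pasteur Inc., Swiftwater, PA) in Stages A and B" (Section 9.1.2). Stage C-1b uses RT 23 at 2 TU.

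For Stage C-1 the protocol gives two accounts. The Protocol Summary states that "Tuberculin/PPD dose has been decreased from 5TU to 2TU for the remainder of Stage C-1 and for Stage C-1b", on the basis of findings in subjects already tested in C-1. Section 9.3.1 fits that account: tuberculin practice used Tubersol "in training for Stages A, B and C-1 or RT 23 SSI", with RT 23 reserved for C-1b. Five other sections give C-1 as 2 TU without qualification:

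- Section 3.3: RT 23 from "Statens Serum Institute, Copenhagen, Denmark in Stages C-1 and C-1b".
- Section 8.2.2: each C-1 subject receives "one of each high dose from each test antigen, and one of 2TU Tuberculin/PPD".
- Section 9.1.2: RT 23 at 2 TU in both C-1 and C-1b.
- Section 9.3.3: each subject receives one dose level of both antigens "and 2TU tuberculin/PPD, RT 23 SSI, Statens Serum Institute, Copenhagen, Denmark".
- Section 13.3: C-1 volunteers receive both antigens at the high dose "and PPD at 2TU, while volunteers from stage C-1b will receive the same antigens".

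Section 13.7 adds that "Stage A, B, and C-1 was completed prior to the amendment of this protocol", so the split of C-1 between the two doses was already known.

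Three planned uses of PPD can span the stages. Section 3.2 compares antigen sensitivity and specificity with PPD in leprosy patients, contacts and unexposed subjects, and Section 3.4 pools A and B for comparison with Stage C. Section 13.1.2 (Stage B) plans to combine PPD responses with those of an equivalent Stage C group to set a cut-off. Section 4.6 lists PPD reaction as a candidate covariate in every group.

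**The concern.** A sensitivity/specificity pair is meant to describe one test. If PPD specificity comes from non-contacts at 5 TU and PPD sensitivity from Stage C subjects at 2 TU, the pair describes two products. Any PPD difference between non-contacts and the Stage C groups could then reflect exposure, preparation or both. PPD is the comparator against which the leprosy antigens' specificity is to be judged (Section 10.1), so a mixed pair could make the antigens look better or worse than they are. The five unqualified dose statements hide the one set of subjects, early C-1, that shares a dose with the non-contacts. The statistical design section is among the five.

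**Working it through.** **1. Enrolment.** Section 13.7 gives 10 + 90 + 80 + 80 = 260, which reproduces the stated total.

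**2. Group by PPD preparation.** From the stage tables in the Protocol Summary and Sections 5.1.4, 9.1.2 and 13.3, with m the unstated number of early C-1 subjects per group on 5 TU:

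| Group | 5 TU | 2 TU, C-1 | 2 TU, C-1b |
|---|---|---|---|
| Non-contacts | 100 | 0 | 0 |
| Contacts | m | 20 − m | 20 |
| BL/LL | m | 20 − m | 20 |
| BT/TT | m | 20 − m | 20 |
| TB | m | 20 − m | 20 |

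m may differ by group. Across C-1, the wording implies at least 1 and at most 79 of 80 subjects on 5 TU. That the early product was Tubersol is inferred from the Protocol Summary with Section 9.3.1; the 5 TU dose is explicit.

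**3. Aliasing.** Take a linear model with an intercept, four group indicators (against non-contacts) and a preparation indicator (1 = 2 TU), six columns in all.

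- A/B plus C-1b: rank 5 of 6.
- A/B plus all 2 TU Stage C data: rank 5 of 6.
- A/B plus all of Stage C, if C-1 really had been all 2 TU: rank 5 of 6.
- A/B plus all of Stage C with early 5 TU subjects identified (5 per group assumed): rank 6 of 6.

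In the first three, the preparation column equals the sum of the four Stage C group columns, so no modelling of those data separates the two.

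**4. What the early C-1 subjects buy.** Assume SD = 1, no losses, equal m per group and one preparation effect common to all groups, including non-contacts. Let p = (40 − m)/40 and I = 4·m(40 − m)/40. The variance of a Stage C group versus non-contact contrast is 1/40 + 1/100 + p²/I. Ignoring preparation, the SE is √0.035 = 0.187.

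- m = 1: I = 3.9, p = 0.975; SE = √(0.035 + 0.2438) = 0.528.
- m = 5: I = 17.5, p = 0.875; SE = √(0.035 + 0.0438) = 0.281.
- m = 15: I = 37.5, p = 0.625; SE = √(0.035 + 0.0104) = 0.213.

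Without the common-effect assumption, only the same-dose contrast remains, with SE √(1/100 + 1/m): 0.458 at m = 5 and 0.277 at m = 15.

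**5. Possible size, by assumption only.** Suppose PPD size is normal, half of non-contacts lie below the cut-off, and preparation shifts PPD size by d SD. The proportion below the cut-off becomes Φ(d): 0.50, 0.60 and 0.69 for d = 0, 0.25 and 0.5. If PPD and antigen sizes correlate at r = 0.3 to 0.5, adjusting an A/B-versus-C antigen contrast for PPD moves it by r·d: 0, then 0.075–0.125, then 0.15–0.25 SD.

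**6. What stays sound within one preparation.** For a paired antigen-versus-PPD difference in proportion positive with discordant proportion D and no true difference, the 95% half-width is 1.96√(D/n). After 10% loss, non-contacts give n = 45 per antigen and C-1b gives n = 18 per group. With D assumed at 0.2 to 0.5, the half-width is 0.13–0.21 at n = 45 and 0.21–0.33 at n = 18. These figures show the precision of the analyses that survive, not the size of the defect.

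**The case against.** The strongest reply is that this is an amendment slip with little analytic consequence. Four parts of it stand.

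- **Records.** A reader might infer that an analyst would label early C-1 readings as 2 TU. The documents make that unlikely: vials are coded (Sections 9.1.1 and 17.5), the vial number is recorded at administration (Section 8.2.2), and dispensing is logged by vial and study day (Section 9.4). Product identity comes from those records.
- **Main comparison.** Sections 4.1 and 10.1 describe comparing PPD and antigen diameters in all subjects. Done within subject and within one preparation, that is sound. Section 13.9.3 bases the detailed accuracy work on the test antigens and specifies no PPD ROC curve or cut-off.
- **Section 13.1.2.** The main fault of the planned PPD combination is that Stage C contains no non-contacts, so the equivalent group does not exist. Preparation is secondary there.
- **Covariate.** A reader might conclude that PPD must be dropped from models spanning A/B and C. That goes too far: Sections 10.1 and 13.2 use PPD as the measure of BCG, tuberculosis and environmental exposure, so dropping it could remove useful adjustment. Section 4.6 also enters it only if it passes a univariate screen.

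One part fails. The five sections cannot be read merely as the current regimen: Sections 8.2.2 and 9.3.3 speak of each individual, and C-1 was already complete. Section 3.2 also names unexposed subjects in the PPD accuracy comparison, and these exist only at 5 TU.

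**Conclusion.** The point holds in limited form. Five sections misstate the C-1 tuberculin dose, and the number on 5 TU is missing. A PPD accuracy comparison using A/B non-contacts and 2 TU Stage C subjects is fully aliased with preparation: 0 of 100 non-contacts had 2 TU. Identified early C-1 subjects restore estimability only partly, at a cost in precision that depends on an unstated count and on assuming the same preparation effect in non-contacts.

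Two stronger readings are not supported. One is that the two preparations are known to give different reactions: the protocol calls the change a decrease prompted by findings but gives no effect size, and the effect may be zero. The other is that the leprosy antigens' own accuracy is compromised: estimates that do not adjust for PPD do not involve the tuberculin product. PPD contrasts within C-1b and within-subject antigen-versus-PPD contrasts inside one preparation are also untouched. Because a secondary objective is affected, this should be corrected, but it does not threaten the primary results.

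**What to change.** - Correct Sections 3.3, 8.2.2, 9.1.2, 9.3.3 and 13.3 to say that early C-1 subjects received 5 TU, and give the number per group.
- Analyse PPD by the product and dose actually given, taken from the vial records.
- Report antigen-versus-PPD comparisons within one preparation: A/B at 5 TU and Stage C at 2 TU by antigen dose. Show early C-1 5 TU subjects separately; they can serve as a same-dose comparison with A/B.
- Do not present non-contact PPD specificity at 5 TU and Stage C PPD sensitivity at 2 TU as one test's performance.
- Remove PPD from the Stage B cut-off combination in Section 13.1.2, since Stage C has no equivalent group.
- Where PPD is a covariate in a model spanning A/B and C, keep it, report the estimate with and without it, and note that its scale changes with preparation.

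The cost is wording and analysis only. No single-preparation PPD sensitivity/specificity pair with unexposed negatives can be reported except from the early C-1 5 TU subjects, and splitting C-1 by preparation leaves smaller PPD subsets.
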